#### Control arm

Usual practice on alcohol health education as delivered normally to all students, including in PSHE lessons and curriculum delivered by class teachers, and usual individualised support for young people with an identified alcohol concern. Young people in the control arm will also be given a healthy lifestyle information leaflet (not containing advice about alcohol) with local sources of help, by the trained staff. Usual practice may vary from school to school and information related to this will be captured by researchers at both time points of the study.

#### Intervention

In addition to input equivalent to the control arm, young people who are eligible and assent to participate will take part in a single 30 min personalised interactive worksheet-based session that was developed during the pilot feasibility trial. This brief intervention is grounded in psychological theory and broadly based on social learning theory which views behaviour as a dynamic interaction between the individual, behaviour and environment. As such, the intervention focuses on personal and contextual factors related to drinking behaviour.^16^ This will be delivered by the trained staff (at school) and will contain personalised feedback about the individual student's drinking behaviour, and behaviour change counselling which encompasses the elements of the FRAMES approach and helps the young person to talk through: how much they drink; how many units are in their drinks; who with, where and why they drink; when they might feel at risk from drinking; what they think are the positive and negatives to drinking; what they perceive others to think about their drinking; whether they would reduce their drinking, why and why not; and what they could do about their drinking (20). The intervention also includes advice about the health and social consequences of continued risky alcohol consumption and a leaflet on alcohol.

#### Randomisation

Neither the learning mentor nor the young person will know which arm they are randomised to until after they assent to take part in the trial. Young people will be individually randomised in a 1:1 ratio to the intervention and control arms. A statistician not otherwise involved with the study will produce a computer-generated allocation list to ensure allocation concealment. All efforts will be made to conceal allocation to young people, school staff (except LM delivering the sessions) and research staff, but we are unable to guarantee that young adults will not discuss their allocation with each other.

### Safeguarding

Should issues arise that concern learning mentors or research staff (eg, alcohol and mental health issues), confidentiality will be broken and the necessary support provided to the young person. Safeguarding issues will be recorded in the trial database. Confidentiality will not be broken otherwise, and school staff will be informed through training that they must work to the same rules as doctors and nurses, meaning that confidentiality can only be broken without consent in exceptional (safeguarding) circumstances. Research/trial staff will provide assistance and support on this issue throughout the trial.

### Recruitment, assent and screening

#### Recruitment

In each of the four geographical sites, initially school performance league tables^28^ will be reviewed and schools from the top, middle and bottom of the league table will be contacted. Snowball sampling will allow contact with potential schools via relationships with recruited schools, although may bias the sample and reduce generalisability of results. That said, efforts will be made to recruit a cross-section of schools, including academy schools, schools in deprived areas and religious schools. Gatekeepers and key personnel (eg, School Board of Governors; County Council contacts) will be approached to suggest—and create an initial contact—with potential schools.

#### Option to opt-out of screening (assent)

In advance of screening, all parents/caregivers (hereafter referred to as ‘parents’) will be informed by letter, sent by the school, that young people will be screened as part of the study within their child's school. Parents will have the choice to opt their child out of the study by completing an opt-out form and sending this (in the freepost envelope provided) to the coordinating research centre at Teesside University. Those young people whose parents have opted them out of the study will not complete the questionnaire. If the opt-out is received after the questionnaire is completed, the questionnaire will be removed from the trial. Additionally, where possible, young people who have been opted-out will not be in the classroom at the time the questionnaire takes place. Obtaining assent to take part in this manner is a method widely used in various national youth questionnaires of alcohol consumption and other health behaviours.^29^

#### Screening for the trial

A video-clip will be played to the young people opted into the study, in each school, to give instructions on completing the questionnaires (see: https://www.youtube.com/watch?v=2ZBm3VZVtx0&feature=em-upload_owner). This video-clip will only provide guidance on the process of questionnaire completion and not on the content. Young people will be asked to voluntarily leave their name and class on the questionnaire. Young people will have the option to: (a) not complete the questionnaire (indicative of lack of assent to screening from the young person); (b) complete the questionnaire anonymously; and (c) complete the questionnaire adding their name and class. Each young person will place their completed questionnaire in an envelope and then return it to the teacher. Teachers will not open these envelopes. Individual responses will not be shared with the class teacher or learning mentor. The Research Coordinator will collect the sealed envelopes from the school. Those young people who have screened positively on the A-SAQ (see below) and have left their name will be eligible for the trial. Completed baseline questionnaires by trial participants will be used for the baseline measurements.

### Data collection

#### Baseline data collection

The study envelope will contain a series of questionnaires, including the study screening questionnaire (part of the A-SAQ): ‘In the last 12 months how often have you drunk more than 3 units of alcohol?’ with the response options of ‘Never’; ‘less than 4 times’; ‘4 or more times but not every month’; ‘at least once a month but not every week’; ‘every week but not every day’; ‘every day’. Scoring ‘4 or more times’, or more frequently, indicates a positive screen and eligibility for the trial. This score was shown in our pilot feasibility trial to be a methodologically robust approach to identifying the adolescent population who may benefit from an intervention.^14^ The A-SAQ will be embedded within a larger questionnaire with items addressing a number of health and lifestyle topics (described above).

#### Invitation to meet with learning mentors

Completed baseline questionnaires will be enclosed in a sealed envelope and returned to the individual universities coordinating each study site. The A-SAQ will be scored and a list of ID numbers and names of those who score positive will be sent to a researcher at Teesside University. After learning mentor training (convened by study site coordinators), learning mentors will be given case packs for each eligible young person. Learning mentors will invite young people who scored positive on A-SAQ on the baseline questionnaire to a meeting with them in their office, where they will open the case pack. In the case pack there will be an information leaflet, a case diary, assent forms and a sealed envelope that contains the randomised condition (intervention or control). Young people will be informed that participation is voluntary and will be given the information leaflet to read before signing the assent form. The assent form also asks for the first part of the young person's postcode. The postcode information will be used to enable a stratified sample of young people to be invited to take part in the qualitative study. Once a young person has assented, the second envelope will be opened which will state whether the participant has been randomised to intervention or control. The learning mentor will then deliver the brief intervention or give the participant the control leaflet (in the same meeting). The completed case packs will be sealed and returned to coordinating sites, then couriered to Teesside University. At all times, only the randomisation statistician (AB), two researchers (JB, LA), and individual learning mentors who meet with the young people will know of the randomisation allocations before the trial ends.

#### 12-Month follow-up

Follow-up will occur 12 months post intervention. All young people who are randomised into the trial will be invited to meet with the Research Coordinator (in school) where they will be asked to complete the same questionnaires used at baseline. The researcher will be blinded to the condition the young person was allocated to. The TLFB (including the primary outcome measure of total alcohol consumption) will also be completed face-to-face in schools with the researcher in order to limit bias in the results. All trial participants will be given an admit-one cinema voucher, to compensate them for their time involved in the study.^30^ Trial participants' baseline and follow-up questionnaires will be linked with a unique ID (the screening number). All participants will be asked by the researcher at follow-up whether they are willing to be contacted for an in-depth interview by a researcher who may be the same individual or another researcher.

#### Intervention fidelity

It is important to ensure learning mentors deliver the intervention in accordance with the intervention manual. To establish intervention fidelity, we will complete competency and fidelity checks at two time points: (1) competency checks of learning mentor training, and (2) fidelity checks of cases delivered during the intervention phase. For the competency checks, each learning mentor will have one simulated intervention with another learning mentor or the research coordinator. Of these sessions, at least 80% will be recorded and ‘signed off’ by an independent expert rater from the research team using the BECCI rating scale.^31^ Additionally, we will attempt to assess 20% of live cases for fidelity (using a pragmatic sampling approach). The BECCI scale is a tool that measures the skills involved in behaviour change counselling. It is scored 0–4 with a score of 2 or more (skills used to ‘some extent’) being acceptable as used in previous studies.^14^
^32–34^ The young people will provide assent for the live case recording to take place. As the recording and analysis of the delivery of the intervention sessions forms part of the employment contract of the learning mentors, formal consent is not required.

#### Sample size calculation

Using estimates from the pilot trial (mean year group size=210, 87% completing baseline questionnaire, 20% being positive on A-SAQ and leaving contact details, 80% recruited to trial and 88% providing data at 12 months follow-up), achieving follow-up data on 235 young people per arm the sample size has been calculated to have a 90% power to detect a standardised difference of 0.3 (which equates to a ratio of 1.5 in geometric means in total alcohol units in 28 days) using a significance level of 5% (figure 1).

**Figure 1 BMJOPEN2016012474F1:**
[figure not shown]
Study flowchart.

### Analysis

#### Baseline data

Descriptive statistics (comparisons of percentages, means or medians as appropriate) will be used to report the pupil-level baseline data, and completeness of intervention received between those allocated to the two trial arms.

#### Primary outcome

The primary effectiveness analysis will be by intention-to-treat. Multiple linear regression will be used to compare the primary outcomes between the two randomisation groups at 12 months, adjusting for any imbalance in key covariates, including school.

#### Secondary outcomes

The secondary outcomes will be analysed in a similar manner. Comparisons of means will be presented as mean differences or ratios of geometric means (if a logarithmic transform is necessary for skewed data) with 95% CIs  ORs and 95% CIs will be presented for binary outcomes. Exploratory analyses will also be undertaken, for example, to examine differences in outcome by gender, deprivation and extent of intervention received, though there is limited power to investigate these comparisons. These moderators have been included so as to consider whether the ABI may need to be targeted when delivered, should it be shown to be effective. We will consider any difference in attrition rates, and any non-randomness of the attrition, when comparing outcomes between the two groups. The pattern of missing observations because of loss to follow-up will be examined to determine the extent of missingness, and whether it is missing at random or is informative. If data are missing to a sufficient extent, the use of appropriate multiple imputation techniques will be considered.

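### Extent of intervention received is listed as a moderator for considering targeting, although it arises after randomisation and has no comparable value in the control arm

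*Protocol article*

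**What the plan says.** The protocol article, Analysis, Secondary outcomes, gives as its examples of exploratory work a plan "to examine differences in outcome by gender, deprivation and extent of intervention received". It concedes in the same sentence that power for this is low. The next sentence gives the purpose: "These moderators have been included so as to consider whether the ABI may need to be targeted when delivered", on the condition that the intervention is found to be effective.

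Three other places bear on this:

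- Intervention: pupils in that arm "will take part in a single 30 min personalised interactive worksheet-based session", on top of input equivalent to the control arm. They also get a leaflet on alcohol.
- Invitation to meet with learning mentors: "Once a young person has assented, the second envelope will be opened which will state whether the participant has been randomised to intervention or control". In that same meeting the mentor either delivers the session or hands over the control leaflet.
- Analysis, Primary outcome: "The primary effectiveness analysis will be by intention-to-treat".

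**The concern.** A moderator is a characteristic that exists independently of allocation and across which the treatment effect may differ. Gender and deprivation qualify. How much of the session a pupil receives does not: it follows allocation and depends on the pupil's engagement and on the mentor.

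Two things follow without any assumed number. First, an arm-by-extent interaction cannot be estimated, because control pupils have no comparable value of extent; the direct comparisons that remain are not randomised. Second, extent of receipt is unknown at the moment a school decides whom to offer the session, so it cannot say whom to target, whatever the data show.

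At stake is an apparent dose-response that reflects who engaged rather than what the session did, read alongside valid subgroup results as if it were of the same kind.

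**Working it through.** **1. Timing and availability of the three variables**

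| Variable | Fixed before allocation? | Comparable in both arms? | Known when deciding whom to offer it to? |
|---|---|---|---|
| Gender | Yes | Yes | Yes |
| Deprivation | Yes | Yes | Yes |
| Extent of session received | No, follows opening of the envelope | No, controls get a leaflet and usual practice | No |

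The Baseline data paragraph of the Analysis section says completeness of intervention received will be described for both arms. For controls this can only mean the leaflet or usual input, so it gives no comparable measure of the session.

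**2. The plan's own figure.** For 90% power, 5% two-sided significance and a standardised difference of 0.3, the normal approximation gives 234 per arm and the t-based calculation 234.5, so the stated 235 is reproduced. The article equates 0.3 SD with a ratio of geometric means of 1.5, which implies an SD of log units of ln(1.5)/0.3 = 1.35. This point does not alter the sample size.

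**3. Form of the bias.** Suppose no treatment effect. Let p be the share of the intervention arm receiving the full session and d the underlying difference, partial minus full receivers.

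- Within the arm, full minus partial = −d. This is the assumption restated, not a result.
- Randomisation makes the arm mean equal the control mean m, so p × (full mean) + (1 − p) × (full mean + d) = m. Hence full mean − m = −(1 − p) × d.

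With p = 0.8, d = 0.3 gives 0.2 × 0.3 = 0.06 SD and d = 0.5 gives 0.2 × 0.5 = 0.10 SD. If heavier drinkers receive more of the session, d is negative and the bias reverses. If the session does work, the same terms are added to the true effects.

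**4. Illustration.** Simulation with zero effect, 235 per arm, 4,000 trials per setting, and the tendency to full receipt negatively correlated with underlying drinking. The correlations and receipt shares are assumptions; the documents give neither.

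| p | Correlation (size) | Full − partial, SD | As ratio of geometric means | Rejected at 5% | Full − all controls, SD | (1 − p) × d |
|---|---|---|---|---|---|---|
| 0.5 | 0.1 | −0.161 | 0.804 | 24.1% | −0.080 | 0.081 |
| 0.5 | 0.3 | −0.477 | 0.525 | 96.1% | −0.241 | 0.239 |
| 0.8 | 0.1 | −0.177 | 0.787 | 19.7% | −0.034 | 0.035 |
| 0.8 | 0.3 | −0.524 | 0.493 | 91.3% | −0.104 | 0.105 |
| 0.9 | 0.1 | −0.191 | 0.772 | 15.9% | −0.022 | 0.019 |
| 0.9 | 0.3 | −0.581 | 0.456 | 79.2% | −0.060 | 0.058 |

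With zero correlation the within-arm test rejected in 5.5% to 6.1% of trials. The intention-to-treat difference stayed within 0.002 SD of zero in every setting.

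**The case against.** The strongest reply is that this is a loose label on a minor analysis. Much of that stands.

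- **A reader might infer that the plan commits to acting on the result.** It does not. It speaks only of considering whether targeting may be needed, within exploratory analyses, and only if the intervention is effective. With no effect at all, that condition would normally not be met. The selection bias would still distort the extent comparison if the intervention did work.
- **A reader might infer a definite bias as large as the 0.3 SD design effect.** The documents give no receipt rate and no link between receipt and drinking, so no such figure can be claimed.
- **Receipt may hardly vary.** One session in the same meeting as the assent leaves little room for non-receipt. As p approaches 1, the bias against controls approaches zero. The comparison by extent then becomes uninformative, not valid.
- **No model is specified.** The article says only that outcome differences by extent will be examined, and an unseen analysis plan could use a complier analysis. That would estimate an effect among receivers; it still would not turn receipt into a moderator. The classification and its targeting purpose are stated in the article, so this is not a complaint about missing detail.

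The article's admission of limited power does not answer the point: it concerns precision, whereas the problem is bias. Adjusting for school would not remove selection among pupils.

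**Conclusion.** The point holds as a fault in how one exploratory analysis is classified and used. That extent is unsuitable as a moderator, and uninformative for targeting, follows from the article's description of the design and needs no assumed figure. The size of the bias does depend on assumptions: d within the intervention arm and (1 − p) × d against all controls, with both quantities and the direction unknown. The intention-to-treat primary analysis and the 235 per arm are untouched. It is worth correcting because the remedy is nearly free; it does not threaten the trial's main conclusion.

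**What to change.** Confine the term moderators, and any statement on targeting, to baseline variables (gender, deprivation), tested as arm-by-covariate interactions. These remain exploratory. For a 50:50 split the standard error is √(4/117.5) = 0.184 SD, so power for an interaction of 0.3 SD is about 37%, and about 0.60 SD is needed for 90%.

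Move receipt to a separate exploratory adherence analysis:

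- If session delivery is recorded and enough pupils did not receive it, estimate a complier average causal effect with randomised arm as instrument, on the primary model's outcome scale and with its covariates. State the assumption that allocation has no effect in non-receivers. The alcohol leaflet given in the intervention arm makes this assumption open to question.
- Otherwise, describe receipt within the intervention arm, with no causal or targeting claim.

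First confirm that delivery is recorded. The article describes the learning mentor case diary as capturing resource use for the economic analysis and does not say that it records session completion.

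The cost is a sentence or two of text and at most one extra exploratory model with wide confidence intervals. If nearly everyone receives the session, that model will come close to repeating the intention-to-treat result.

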#### Health economics

The economic component will include a within trial cost-utility and cost-consequence analysis and, as described below, a model based analysis taking the perspective of the UK public sector (NHS, educational, social and criminal services). The cost-utility analysis will use measures of effectiveness limited to health-related quality of life as measured by EQ-5D Y. The cost-consequence analysis will take the same perspective for costs but will present these alongside all of the primary and secondary measures of effectiveness outlined above. The follow-up for the within trial analyses will be 12 months, so discounting will not be conducted. For the model-based analysis, the time horizon will be longer (potentially up to the participant's life time) and costs and effects will be discounted at 1.5%, the UK recommended rate for public health interventions,^35^ with a sensitivity analysis used to explore the impact of higher (and lower) discount rates.

#### Within-trial analysis: cost-utility and cost-consequence analyses

For each trial participant, the use of health, educational, criminal and social care services will be elicited using the S-SUQ administered at baseline (with a recall period of 3 months) and 12 months. Further cost data will come from the learning mentor time case diaries completed by the learning mentors for each contact. Costs for healthcare and social services will be obtained from standard sources such as NHS reference (http://www.gov.uk), the British National Formulary^36^ for medications, Unit costs of Health and Social Care^37^ for contacts with primary care. Further data will come from the study centres themselves. Data on the use of educational services will be elicited via the questionnaire. As part of the pilot trial, we confirmed with the expert group the type of services relevant to collect and have also added further questions related to days missed from school and truancy.

Learning mentor training costs will be included and will need to be apportioned according to scaled up practice. This will be informed by data from the training conducted as part of the trial and through expert opinion. The time of educational staff will be sought through a parallel costing exercise in which these staff will be asked to provide information on the impact of the intervention on their workload. With respect to learning mentors, a detailed proforma (case diary) was developed and tested in the pilot to capture resource use for cost-effectiveness analyses, and this new tool will be used in this study. With respect to school building and other large capital items, the opportunity cost will be considered. Some resources (eg, buildings) will exist with or without the intervention and the intervention may not displace any other activity. In this circumstance, the opportunity cost of the building would be zero. However, costs might be incurred in terms of heat, power and light, and these data will be captured using standard costing methods.^38^ For each participant, measures of use of resources will be combined with unit costs to provide a cost for that participant. We anticipate that the price year adopted for the base case analysis will be 2017 when the final analysis is conducted.

The EQ-5D Y will be administered at baseline and 12 months with UK population tariffs^39^ used. Health state utilities from the EQ-5D Y will then be used to estimate QALYs using the area under the curve approach.^26^

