^25^Two questions relating to sexual risk taking are included. These are the same questions as in the pilot study.^14^ These questions are: ‘After drinking alcohol, have you engaged in sexual intercourse that you regretted the next day?’ and ‘After drinking alcohol, have you ever engaged in sexual intercourse without a condom?’ Both questions can be answered with one of the three following options: ‘I have never engaged in sexual intercourse’, ‘Yes’, or ‘No’;Energy drink consumption will be assessed by asking young people how many times a week they consume energy drinks. Young people can answer: ‘never’, ‘less than once a week’, ‘2–4 days a week’, ‘5–6 days a week’, ‘every day once a day’ and ‘every day more than once a day’;Age of first smoking and how many cigarettes were smoked in the past 30 days;^1^Demographic information collected will include gender and ethnicity. The first part of the postcode will be collected for trial participants;Quality of life measured using the EQ-5D Y, which is a valid measure for those aged 12 or older, and will be used to measure health-related quality of life.^26^ Responses to the five items will be converted into utility scores using the UK population algorithm. This will be administered at baseline and 12 months post intervention;^26^Quality-adjusted life years (QALY) estimated using general population tariffs from responses to EQ-5D Y administered and scored at baseline and 12 months.

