#### 12-Month follow-up measurements

All tools assessed at baseline;Per cent days abstinence over last 28 days, drinks per drinking day and days>2 units from 28 day TLFB;Incremental cost per QALY gained at 12 months;Depending on findings, modelled estimates of incremental cost per QALY and cost-consequences in the longer term;National Health Service (NHS), educational, social and criminal services data estimated using a modified S-SUQ^27^ and a learning mentor case diary developed in the pilot study, measured at 12 months post intervention;Cost-consequences presented in the form of a balance sheet for outcomes at 12 months. (For further details, see online supplementary appendix 1).

10.1136/bmjopen-2016-012474.supp1supplementary appendix

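### Half of each QALY is a pre-randomisation utility, and the printed adjustment rule does not guarantee a baseline-utility term in the incremental QALY

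*Protocol article*

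**What the plan says.** Four parts of the protocol article bear on this.

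- **How the QALY is built.** The section *Within-trial analysis: cost-utility and cost-consequence analyses* states: "The EQ-5D Y will be administered at baseline and 12 months with UK population tariffs". It continues: "Health state utilities from the EQ-5D Y will then be used to estimate QALYs using the area under the curve approach". *Health economics* adds: "The follow-up for the within trial analyses will be 12 months, so discounting will not be conducted".
- **When baseline is taken.** *Screening for the trial* states: "Completed baseline questionnaires by trial participants will be used for the baseline measurements". That questionnaire precedes the meeting with the learning mentor, where the allocation envelope is opened after assent (*Invitation to meet with learning mentors*).
- **Where the QALY sits among the outcomes.** *Baseline secondary outcome measurements* lists: "Quality-adjusted life years (QALY) estimated using general population tariffs from responses to EQ-5D Y administered and scored at baseline and 12 months". *12-Month follow-up measurements* lists: "Incremental cost per QALY gained at 12 months".
- **How outcomes are compared.** Under *Analysis*, *Primary outcome* specifies multiple linear regression, "adjusting for any imbalance in key covariates, including school". *Secondary outcomes* extends the same approach to the secondary outcomes. Baseline utility is not named as a covariate in either place. The economic sections name no between-arm estimator at all, adjusted or unadjusted.

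**The concern.** For most outcomes, baseline adjustment gains precision only as far as the baseline value predicts the later one. The two-point QALY is different, because the baseline utility is an arithmetic part of the outcome. The intervention cannot change that part, and its spread between pupils enters the QALY directly. An unadjusted contrast therefore carries half of any chance baseline difference between the arms. It also loses precision even when baseline utility does not predict 12-month utility.

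A rule that adjusts only when imbalance is seen does not deal with this. When the arms look balanced, the adjusted and unadjusted point estimates nearly agree, but the unadjusted standard error still contains the baseline variance, so the reported interval is wider than it need be.

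Cost-effectiveness is part of the stated research aim, and the cost per QALY is a listed 12-month measure. The article gives no expected QALY effect. If the true effect is of the same order as the baseline noise computed below, that noise could determine the sign of the incremental QALY.

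**Working it through.** **Inputs from the article.** Two utility times, 12 months apart; area under the curve; no discounting; 1:1 allocation; 235 followed up per arm.

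**Inputs not in the article, so assumed.** The utility SDs s0 (baseline) and s12 (12 months), and the correlation r between them. Ranges are shown.

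**The plan's own figure.** *Sample size calculation* aims at 90% power for a standardised difference of 0.3 at the 5% level. Taken two-sided, n = 2(1.960 + 1.282)²/0.3² gives 234 per arm. The t-based version gives 234.5, rounded up to 235, and power at 235 is 0.902. The 235 reproduces. It concerns the primary outcome; no precision or power is given for the QALY.

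**Step 1: the QALY.** A trapezoid over one year gives QALY = (u0 + u12)/2.

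**Step 2: variance without baseline utility.** Var = (s0² + s12² + 2·r·s0·s12)/4. With s0 = s12 = s this is 0.5·s²(1 + r).

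**Step 3: variance after linear regression on u0.** The u0 half drops out, and so does the part of u12 that u0 predicts. Var = s12²(1 − r²)/4, or 0.25·s²(1 − r²) with equal SDs.

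**Step 4: ratio.** With equal SDs, adjusted over unadjusted variance is 0.5(1 − r). The ratio of standard errors, and so of interval widths, unadjusted to adjusted, is √(2/(1 − r)). With k = s0/s12 in general, it is √[(k² + 1 + 2rk)/(1 − r²)].

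| r | k = 0.8 | k = 1 | k = 1.25 | simulation, k = 1 |
|---|---|---|---|---|
| 0 | 1.28 | 1.41 | 1.60 | 1.41 |
| 0.3 | 1.53 | 1.69 | 1.91 | 1.71 |
| 0.5 | 1.80 | 2.00 | 2.26 | 2.08 |
| 0.7 | 2.33 | 2.58 | 2.91 | 2.57 |

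The simulation used 235 per arm and 2,000 repeats. Mean differences were near zero with and without adjustment, as randomisation implies. At r = 0.5 and k = 1 the variance ratio is 0.25, so adjustment is worth as much as four times the sample for this outcome.

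**Step 5: chance baseline imbalance in QALY units.** The standard error of half the baseline difference is 0.5·s·√(2/235).

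- s = 0.10: 0.0046
- s = 0.15: 0.0069
- s = 0.20: 0.0092

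At s = 0.15 the 95% range is ±1.96 × 0.0069 = ±0.014 QALY, or 0.014 × 365 ≈ 5 days of full health.

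**The case against.** The strongest objection is that this is only silence. The sentence on area under the curve says how each pupil's QALY is calculated, and it is correct. The covariates for the between-arm comparison are the kind of detail a journal article leaves to the full protocol or to an economic analysis plan, and neither is shown. That succeeds against the economic sections taken alone: nothing in them is wrong.

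It does not dispose of the rule the article does print. QALYs are listed with the secondary outcomes, those follow the primary outcome's approach, and that approach adjusts for imbalance. A rule of that form can leave baseline utility out in just the case where the loss is pure precision. It can be argued that those sections were never meant to govern the economic analysis; the point then reduces to asking that the economic plan be confirmed.

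A second objection is that a material baseline imbalance is exactly what the printed rule would respond to. That stands in part. If baseline utility counts as a key covariate, the rule would limit the harm to the point estimate, but it would not recover precision when no imbalance is seen.

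A reader might infer something stronger: that the plan specifies an unadjusted comparison, so its interval will be 1.4 to 2.6 times as wide as necessary. The article does not support that. It never says the comparison will be unadjusted, and the only text that reaches QALYs points to regression. The multiplier also depends on a correlation and an SD ratio that the article does not give.

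**Conclusion.** The point holds in conditional form. It follows from the stated design that half of each QALY is a pre-randomisation value, and the printed adjustment rule does not guarantee that baseline utility enters the model.

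If it does not enter, the interval for the incremental QALY would be about 1.4 to 2.6 times as wide as with it, for equal SDs and r from 0 to 0.7. Over the same r, SD ratios of 0.8 to 1.25 give about 1.3 to 2.9. The direction needs no such assumption: linear regression on u0 cannot raise the residual variance, and the cost of one degree of freedom among 470 pupils is negligible.

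It would be wrong to read this as bias. Under randomisation the unadjusted difference is still centred on the true one; what is lost is precision, with more exposure to chance imbalance. It is an improvement worth making to the printed rule, not an error in the QALY calculation.

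**What to change.** In the within-trial economic section, state that the incremental QALY is always estimated by regressing the 12-month QALY on arm, baseline EQ-5D Y utility and school, whether or not baseline utility looks imbalanced, and that this estimate is the one used in the cost per QALY. If an economic analysis plan already says so, a cross-reference is enough.

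The cost is one sentence and one regression term. Baseline utility is already collected from trial participants, so no new data are needed.
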